### Statistical methods and analysis

The data analysis plan will proceed through data entry and cleaning, missing data management and statistical analysis. All quantitative data will be coded and entered to SPSS Version 25 (SPSS, an IBM company, Chicago, Illinois, USA). The data will be inspected visually with random searches and frequency counts to ascertain its completeness. Demographic and clinical characteristics will be compared using chi-square test (for normally distributed data) or Mann-Whitney *U* test (data that is not normally distributed). Between group differences will be assessed using independent t test (for continuous data). Both per-protocol (PP) and intention to treat analysis (ITT) will be performed respectively on participants who completed the entire intervention and those recruited to participate. Methods for longitudinal data such as generalised estimating equations (GEE) will be employed. All statistical tests will be conducted at 95% confidence interval.

Qualitative data emerging from the follow-up process evaluation phase will be analysed using content analysis [54]. All audio recordings will be transcribed verbatim and translated from Chinese to English using the Trint Automation Software. The transcripts will be inspected for correctness and completeness by two native speakers who are also fluent in English. The final versions will be exported to the NVivo version 10 software for data management and analysis by two researchers with ongoing consultation with the research team. The analytical process will commence with reading all data repeatedly to achieve immersion and obtain a sense of the whole. Then, data will be read line by line to formulate codes by first highlighting the exact words from the text that appear to capture key thoughts. Following this, the researcher will approach each transcript by making notes of initial impressions. Following the formulation of the codes, labels for the code will be formulated directly from the text. At this point, an initial coding scheme will be formulated. Similar codes will be sorted to formulated categories. Emergent categories will be used to organize and group codes into clusters [54].

Data emerging from the quantitative strand will collated into SPSS Version 25. We will employ descriptive statistics to ascertain the distribution of the data.

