**Methods:**

A single-centre, double-arm randomised controlled trial with a process evaluation phase will be utilised for this study. All adult burn survivors aged ≥ 18 years with burn size ≥ 10% total burn surface area at the site during the study period will be screened for eligibility at least 72 h to discharge. A sample size of 150 will be block randomised to treatment (receiving the nurse-led transitional care programme and routine post-discharge service) and control groups (receiving routine post-discharge service). The nurse-led transitional care programme comprises of predischarge and follow-up phases with the delivery of bundle of holistic interventions lasting for 8 weeks. There are three timelines for data collection: baseline, immediate post intervention, and 4 weeks post-intervention.

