### Study outcomes

#### Primary outcome

*Quality of life*: Quality of life which is defined as the adult burn survivors’ perceptions of their health status and well-being is the primary outcome for the trial and will be assessed at baseline (T0), following completion of the intervention at 8 weeks (T1) and at 4 weeks post-intervention (T2). The outcome will be objectively assessed using the Chinese version of the Burn Specific Health Scale-Brief and EQ-5D-5L. The BSHS is an outcome scale designed specifically for burns patients. It comprises of four areas: physical, psychological, social relations, and general health condition that is consistent with the biopsychosocial model. A recent review has suggested that generic scales are more sensitive than the BSHS-B domains from one-month post-burn [37]. Thus, as the study will cover up to 3 months post-discharge, the BSHS-B and EQ-5D will be used to measure quality of life in the study. The BSHS-B comprises of 40 questions, 9 sub-scales, and 3 domains (physical, mental, and social). Internal consistency of the total instrument has been reported to be *α* = 0.94 with test-retest reliability suggesting that the intraclass correlation coefficient (ICC) ranged from 0.81 to 0.96 with a total score of 0.93 [38]. The Chinese version has 38 items with a reported Cronbach alpha 0.97 and split half reliability of 0.98 [39]. The EQ-5D-5L is a generic tool to assess quality of life. The instrument has five dimensions: mobility, self-care, usual activities, pain/discomfort, and anxiety/depression. Each dimension has 5 levels: no problems, slight problems, moderate problems, severe problems, and extreme problems. The EQ-5D-5L is a valid extension of the 3-level system (EQ-5D-3L) which is found to have improved measurement properties, with reduced ceiling effect, strengthened discriminatory power and established convergent and known-groups validity [40].

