## Data collection, management, and analysis

### Data collection methods and management

All outcomes will be assessed at baseline (T0); that is after the patient has been recruited. Following the completion of the intervention, the second phase of data collection (T1) will be undertaken; that is at the 8th week. The third phase of data collection (T2) will be the follow-up phase at 4 weeks post-intervention. Data collection will be in the form of completion of questionnaires. The data collection process will be undertaken by three research assistants who will be blinded to the groups of the participants. The research assistants have completed a 10-h training programme covering the outcome measures to be used. Following the training, they undertook a role play to enable the research team to ascertain the inter-rater reliability/percentage agreement with the following results: Burn Specific Health Scale-B (87.7%), EQ-5D-5L (100%), HADS (92.5%), PSQI (86.7%), DASH (84.4%), VAS (100%), BPI (100%), and VSS (100%). All quantitative data will be entered and stored in SPSS Version 25 (SPSS, an IBM company, Chicago, Illinois, USA). All hard copies of documents relating to the study will be stored under lock and key only accessible to designated research team member.

For the follow-up process evaluation phase (qualitative strand), face to face semi-structured interviews with an interview guide will be utilised to collect data after the intervention period has elapsed. Topics for the interview guide will be based on the process evaluation components as highlighted in Table 1. All interview proceedings will be audiotaped and transcribed verbatim in the Trint Automated Transcription Software. Interview transcripts will be exported to QSR NVivo version 10 will be used to manage the data. All soft files related to the study will be kept in a password protected computer only accessible to the principal investigator and the doctoral student investigator. Paper files will be kept under lock and key. For the quantitative phase, we will review the recruitment, enrolment, and follow-up records.

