The concept of rehabilitation is still under development in most parts of Mainland China [4, 24, 59, 60]. The escalating chronic disease burden and ageing population further leaves limited resources allocated to burns rehabilitation in Mainland China [60]. Previous studies in Mainland China have highlighted the significant focus on medical management of burn injuries with limited attention to comprehensive rehabilitative support [4, 24]. Thus, service gaps may exist to offer comprehensive rehabilitative support to burn survivors. Meeting this need requires multidisciplinary efforts to ensure that burn survivors and their families receive professional support commensurate to their needs in a continuous and coordinated manner. The nurse-led transitional burns rehabilitation programme (4Cs-TBuRP) will add new knowledge regarding the organization and implementation of professional support for adult burn survivors and their families as well as strengthening post-discharge care at the study hospital. The programme extends the function of burn care nurses into advanced roles regarding coordinating care and delivering advanced burn care support such as scar management in home-based environment. Additionally, the follow-up process evaluation phase will offer insights into the implementation process to understand contextual factors that facilitated or hindered the delivery of the intervention. By combining quantitative and qualitative data, we will attain greater explanatory power and move beyond ‘does it work?’ to ‘what works and for who?’ Based on past trials, an anticipated limitation of this study may be dropout rate. Possible attrition bias will be addressed by examining the extent and reasons for dropout across the intervention and control groups.

In conclusion, the 4Cs-TBuRP offers an opportunity to actively follow-up on burn survivors and their families following discharge and offer professional support within the home environment. This is in response to a global need for continued rehabilitative care for burn survivors following discharge [14]. The telehealth component which reflects the changing nature of healthcare particularly as the world is still navigating through the coronavirus pandemic implies that burn survivors will continue to receive professional support at a distance highlighting the potential benefits of the 4Cs-TBuRP [61, 62].

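### Outcome comparison rests on a t test that cannot adjust for baseline, beside a GEE and two analysis sets, with no method or set named primary

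*Protocol article*

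**What the plan says.** The relevant text is in the protocol article, mostly under Statistical methods and analysis.

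- **Between-arm test:** "Between group differences will be assessed using independent t test (for continuous data"). Neither the visit nor the scale (raw score or change from baseline) is given.
- **Longitudinal method:** "Methods for longitudinal data such as generalised estimating equations (GEE) will be employed". GEE is offered as an example and is not ranked against the t test.
- **Analysis sets:** "Both per-protocol (PP) and intention to treat analysis (ITT) will be performed respectively on participants who completed the entire intervention and those recruited to participate". Neither set is called primary.
- **Baseline:** under Data collection methods and management, "All outcomes will be assessed at baseline (T0); that is after the patient has been recruited".
- **Visits:** the abstract lists baseline, end of intervention (8 weeks) and 4 weeks later. No visit is named primary.
- **Instruments:** under Primary outcome, "the BSHS-B and EQ-5D will be used to measure quality of life in the study". The sample size is based on the burn-specific scale.
- **Attrition:** the sample-size section allows for 20%. The Discussion says "Possible attrition bias will be addressed by examining the extent and reasons for dropout across the intervention and control groups".

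**The concern.** The article does more than leave analysis detail open. It commits to two methods and two sets as equals, and the one test it ties to between-group differences has no place for the baseline value.

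Three things are at stake:

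1. **Precision.** Quality of life at discharge is likely to predict quality of life 8 to 12 weeks later. Adjusting for it shrinks the error variance without using any further patients.
2. **A single answer.** Two methods in two sets give up to four candidate results for each instrument and visit. If they disagree, the article gives no rule for which one answers the primary question.
3. **Selection.** The per-protocol set depends on what happens after randomisation, namely completing the intervention, so membership may be related to outcome. Standing level with intention-to-treat, it could carry the trial's conclusion.

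**Working it through.** **Inputs from the article.** 38 analysable participants per arm in the main trial, before the attrition allowance; 95% confidence level; 90% power; 1:1 allocation; an effect described only as moderate; a non-directional alternative, read here as two-sided 5%.

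**Assumptions, not in the article.** Standardised difference d = 0.5 for a moderate effect. Baseline-to-follow-up correlation r = 0.3, 0.5 or 0.7. Equal variance at baseline and follow-up.

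**The article's own figure.** At d = 0.5, two-sided 5% and 90% power, a two-sample t test needs 85 per arm, not 38. The stated 38 is reached at d of about 0.75, a value the article does not give. That is a separate sample-size question. Here 38 per arm serves only as a common yardstick for comparing methods.

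**Relative error variance** (follow-up-only t test = 1):

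- Baseline-adjusted comparison: 1 − r²
- t test on change scores: 2(1 − r)

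The difference is 2(1 − r) − (1 − r²) = (1 − r)², which is positive for every r below 1. Adjustment is therefore always more precise than a change score. A change score matches the follow-up-only test at r = 0.5 and is worse than it below that.

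**Effective d** = 0.5 / √(relative variance). Power is from the noncentral t distribution with 38 per arm:

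| r | Variance, adjusted | Effective d, adjusted | Power, adjusted | Variance, change score | Effective d, change score | Power, change score |
|---|---|---|---|---|---|---|
| 0.3 | 0.91 | 0.524 | 61.6% | 1.40 | 0.423 | 44.4% |
| 0.5 | 0.75 | 0.577 | 70.0% | 1.00 | 0.500 | 57.6% |
| 0.7 | 0.51 | 0.700 | 85.4% | 0.60 | 0.645 | 79.3% |

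The follow-up-only t test has 57.6% power whatever r is. Adjustment lowers the variance by 9%, 25% and 49% at the three correlations. By the normal approximation, the number needed for 90% power at d = 0.5 falls from 85 per arm to 77, 64 and 43.

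**Number of candidate results.** 2 methods × 2 sets = 4 for each instrument and visit. They are correlated, so treating them as independent tests would overstate the false-positive risk, and no such figure is claimed here.

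**Completer set.** The per-protocol analysis is "performed respectively on participants who completed the entire intervention and those recruited to participate" when read with its intention-to-treat partner: completers for the first, everyone recruited for the second. Completion is a post-randomisation event. Tabulating how many left and why, as the Discussion proposes, describes the loss but leaves the estimate unchanged. The size of any bias cannot be worked out from the article, because it would depend wholly on an assumed dropout model.

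**The case against.** The strongest reply is that the text is less damaging than it first appears. Four stronger readings are tempting, and the article does not support them.

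- **That baseline is certainly discarded.** The t test could be meant for change scores. Its sentence directly follows the one on comparing baseline characteristics and might even belong with it. A GEE fitted over all three visits would use T0. So loss of baseline information is certain only for a t test on follow-up values. What stands is that neither form of t test is as precise as adjustment, and nothing makes the GEE primary.
- **That the analysis uses observed cases only, with an unweighted GEE.** The article lists management of missing data as a step before analysis and assigns intention-to-treat to everyone recruited. Imputation would fit that wording. The method, and the GEE specification, may properly sit in the analysis plan.
- **That per-protocol sets intervention completers against all controls.** The Eligibility criteria section defines dropout as leaving either arm before week 12, and controls have a defined package that includes two social calls. The wording of the set is loose, but that asymmetry is inferred. Post-randomisation selection remains whichever way it is read.
- **That reporting both sets is itself an error.** It is conventional. The fault is that neither is named primary.

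It is also fair to say that the power figures depend on an assumed d and r, and that choosing a mixed model over GEE, a particular visit or further covariates is the analyst's preference. The background frames the question over the first 12 weeks after discharge, so the end-of-intervention visit is not the obvious choice.

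**Conclusion.** The point holds in a limited form. The article names a between-group test that cannot adjust for a baseline it collects, sets it beside a longitudinal method, and gives two analysis sets equal standing, one of them selected after randomisation. No method or set is primary.

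The gain from adjusting, compared with a t test on follow-up values at 38 per arm and d = 0.5, is about 4, 12 and 28 percentage points of power at r = 0.3, 0.5 and 0.7 (61.6, 70.0 and 85.4 less 57.6). Compared with a t test on change scores it is about 17, 12 and 6 points. These sizes rest on the assumed d and r and on equal variances. That adjustment is at least as precise as either t test in large samples does not depend on them. If the GEE turns out to include T0 and to be the primary analysis, most of the precision loss disappears, but the article does not say so. The article does not show that baseline will be thrown away or that the completer analysis will be biased by any particular amount.

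**What to change.** State one primary analysis before outcome data are examined:

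- **Outcome and population:** BSHS-B in all randomised participants, analysed as randomised.
- **Model:** a longitudinal model of the follow-up visits adjusted for baseline BSHS-B. Either a linear mixed model or a GEE with baseline as a covariate would serve, with missing data handled under missing-at-random. For GEE this means weighting or imputation.
- **Contrast:** one time-point comparison, chosen and named in advance by the investigators to match the 12-week question.
- **t test:** not used for outcome comparisons.
- **Per-protocol:** labelled supportive, with completion defined for each arm.
- **Dropout tables:** kept as description and no longer presented as the means of addressing attrition bias.

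The cost is revised wording and slightly more analysis work. T0, T1 and T2 are already collected, so no new measurements are needed.

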## Monitoring

Minimal adverse effects are expected from the proposed intervention. Standardised protocols exist at the study centre regarding the management of known of potential adverse effects such as infection. Adverse events related to the intervention will be monitored through review of the patient’s records, participant self-report, and by the clinicians. All adverse events will be reported to the Institutional Review Board of the Hong Kong Polytechnic University.

### Ethics and dissemination

Ethical clearance for the study has been granted by the Institutional Review Board of the Hong Kong Polytechnic University (HSEARS20200730001). Additionally, the study has been prospectively registered with a trial registry and currently available in public domain (NCT04517721). The IRB and trial registry will be informed of any modifications that may occur during the conduct of the trial. Protocol modifications which affect participants directly after enrolling in the trial will be communicated directly to participants via the research team member. Consent will be obtained from participants before completing the recruitment process. All data emerging from the studies will be kept under lock kept by authorised personnel. Confidentiality and anonymity will be ensured throughout the study. Data emerging from the study will be accessed only by the research and clinical teams. The protocol for this study is publicly available. Additional details will be provided upon reasonable request. Statistical codes for analysis will be published with the final publication of the trial results when completed. De-identified participant-level data may be made available upon reasonable request, after reviewing the request by the study team and the local institution. Trial auditing will be conducted every six weeks by the research and clinical team to ensure adherence/compliance to the protocol. The investigators plan to disseminate the trial results via publication in peer reviewed journals and at conferences. All research and clinical team members meeting authorship criteria will have final authority over manuscript content. The study protocol, if published, will be available in public domain. However, participant-level dataset will be maintained by the research/team which can be made available on reasonable request.

### Ancillary and post-trial care

This is not applicable. No specific provisions for post-trial care were considered in this trial due to the nature of the intervention. All harms and adverse events (AE) will be dealt properly, and if the participants need any health care due to participation in the study, they will be referred to the respective referral services.

## Discussion

Recovery following burns is a complex process with varied biopsychosocial-environmental needs and rehabilitative support commensurate to those needs is very important to ensure optimal recovery of the burn survivors [55]. Recent studies have likened the recovery process following burns to living with a chronic ailment which suggest that a flexible but structured and sustained follow-up plan is required to support the burn survivor and their families [56, 57]. Transitioning from the Burn Unit to the home/community is often chaotic with burn survivors and their families experiencing limited professional support [57, 58]. A lack of continuous and comprehensive support in the early post-discharge period adversely affects patient outcomes, thus creating a critical gap.

The concept of rehabilitation is still under development in most parts of Mainland China [4, 24, 59, 60]. The escalating chronic disease burden and ageing population further leaves limited resources allocated to burns rehabilitation in Mainland China [60]. Previous studies in Mainland China have highlighted the significant focus on medical management of burn injuries with limited attention to comprehensive rehabilitative support [4, 24]. Thus, service gaps may exist to offer comprehensive rehabilitative support to burn survivors. Meeting this need requires multidisciplinary efforts to ensure that burn survivors and their families receive professional support commensurate to their needs in a continuous and coordinated manner. The nurse-led transitional burns rehabilitation programme (4Cs-TBuRP) will add new knowledge regarding the organization and implementation of professional support for adult burn survivors and their families as well as strengthening post-discharge care at the study hospital. The programme extends the function of burn care nurses into advanced roles regarding coordinating care and delivering advanced burn care support such as scar management in home-based environment. Additionally, the follow-up process evaluation phase will offer insights into the implementation process to understand contextual factors that facilitated or hindered the delivery of the intervention. By combining quantitative and qualitative data, we will attain greater explanatory power and move beyond ‘does it work?’ to ‘what works and for who?’ Based on past trials, an anticipated limitation of this study may be dropout rate. Possible attrition bias will be addressed by examining the extent and reasons for dropout across the intervention and control groups.

In conclusion, the 4Cs-TBuRP offers an opportunity to actively follow-up on burn survivors and their families following discharge and offer professional support within the home environment. This is in response to a global need for continued rehabilitative care for burn survivors following discharge [14]. The telehealth component which reflects the changing nature of healthcare particularly as the world is still navigating through the coronavirus pandemic implies that burn survivors will continue to receive professional support at a distance highlighting the potential benefits of the 4Cs-TBuRP [61, 62].

